### Sample size {14}

Sample size calculation was performed according to the primary outcome, using an online power calculator for binary outcome non-inferiority trials (Sealed Envelope Ltd. available from: www.sealedenvelope.com). This is a non-inferiority trial with a binary outcome using a one-sided alpha of 0.05 and 80% power. The assumed success rate is 93.7% in the control arm, based on center-specific experience as well as the literature [13]. Data on the use of L-PRF for this indication is limited, but we assume a 95% success rate based on a prior feasibility study [9].

The statistical hypothesis for testing the treatment difference is presented as follows: H_0_: Δ ≤  − 0.05 tested against the alternative hypothesis and H_A_: Δ >  − 0.05, where Δ is the difference between the success rates of experimental and control condition and − 0.05 is the non-inferiority difference. The non-inferiority limit was set at 0.05 considering (1) reported CSF leakage rates without commercially available fibrin sealant averaging 17.2% [14] and (2) important additional benefits of L-PRF compared to commercially available fibrin sealants including the completely autologous nature (eliminating immune reactions), presence of immunologic cells and reduced costs.

Based on this power calculation, 334 patients need to be included, 167 in each group. A drop-out rate of 2–5% is expected due to loss of follow-up and non-adherence to the allocation or failure of L-PRF preparation. Therefore, 350 patients will be enrolled, 175 in each group.

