## Trial design {8}

This study is a single-blinded, prospective randomized controlled trial with subjects randomized 1:1 in two parallel groups, i.e., experimental (L-PRF treatment) and active control (commercially available fibrin sealants).

In this study, the general objective is to show the non-inferiority of L-PRF as a closure technique compared to commercially available fibrin sealants in supra- and infratentorial surgery. This prospective randomized controlled trial was approved by the local Ethical Committee (UZ Leuven, S61460) and is registered at ClinicalTrials.gov (ID: NCT03812120) [2]. Recruitment started on 06 January 2020.

Demographic data, medical history, and surgical indications are reported prior to surgery. During the hospitalization (from 1 day preoperatively until the day of discharge), vital parameters such as body temperature and blood pressure are monitored, as well as medication intake. Patient’s quality of life (QoL) is questioned using the Research and Development 36-item Short Form Survey (RAND SF-36) and EuroQol Five Dimensions (EQ-5D) questionnaires.

To perform a cost-effectiveness evaluation, all costs and effects will be collected. Additionally, patient’s general quality of life is assessed using the EQ-5D-3L Questionnaire prior to surgery and at the 6–12 weeks follow-up visit (FU3). Complications and adverse events are assessed at the time of surgery, 2 days postop (FU1), at hospital discharge (FU2), and at follow-up visits (FU3) (Fig. 2).

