### Statistical methods

### Statistical methods for primary and secondary outcomes {20a}

Data will be analyzed in the GraphPad Prism software using a simple *t* test, or non-parametric Mann–Whitney *U* test when not normally distributed, with Bonferroni Holm correction for multiple testing. A *p*-value ˂ 0.05 is considered statistically significant. The primary outcome, i.e., CSF leakage, will be analyzed in terms of a difference in risk between the two treatment groups. The mean difference between the two treatment groups will be reported as a two-sided 95% confidence interval. Secondary endpoints will be calculated using a simple *t* test, non-parametric Mann–Whitney *U* test when not normally distributed, Fisher’s exact test, or chi-squared test, based on the number of events.

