## Discussion

The design and rationale of a prospective randomized clinical trial studying the role of L-PRF in cranial dural closure are discussed. The primary aim of the study is to investigate the non-inferiority of L-PRF compared to commercially available fibrin sealants, the current standard of care. Additionally, we assess the safety and cost-effectiveness of L-PRF for dural closure in cranial surgery. The results of this trial will provide further insight into the efficiency of dura closure. As CSF leakage is an important complication of cranial surgery, this study is of major importance to the field of neurosurgery. Some preliminary pilot studies reported the feasibility of L-PRF as a closure aid in neurosurgery [9, 16]. L-PRF has been reported to enhance wound healing by providing growth factors to the surrounding tissue [17, 18]. This study represents the first large-scale randomized controlled trial comparing L-PRF to the current standard of care. With the intended sample size, we believe to be able to show the non-inferiority of L-PRF with respect to CSF leakage. The results of this trial can impact future decision-making for dura closure in cranial surgery.

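### The trial is sized at one-sided alpha 0.05, but the only interval given for the primary difference is a two-sided 95% CI; the plan does not say which bound decides non-inferiority, and the two can disagree at the leak rate it expects

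*Protocol article*

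**What the plan says.** All references are to the protocol article.

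- **Sample size {14}**: "This is a non-inferiority trial with a binary outcome using a one-sided alpha of 0.05 and 80% power". The null hypothesis is that the success rate on L-PRF minus that on control is -0.05 or lower. The planning rates are "The assumed success rate is 93.7% in the control arm" and, for L-PRF, "we assume a 95% success rate based on a prior feasibility study". The result is "334 patients need to be included, 167 in each group", raised to 350 (175 per arm) for drop-out.
- **Statistical methods for primary and secondary outcomes {20a}**: the primary outcome is analysed as a difference in risk, and "The mean difference between the two treatment groups will be reported as a two-sided 95% confidence interval". The same section sets a general significance threshold of p < 0.05, sidedness not stated, for t or Mann-Whitney tests.
- **Outcomes {12}**: the success rate in each arm is also given with a 95% interval.
- **Discussion**: "With the intended sample size, we believe to be able to show the non-inferiority of L-PRF with respect to CSF leakage".

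The article mentions neither a 90% interval nor a one-sided 95% bound, and it does not say which limit is compared with -0.05.

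**The concern.** A one-sided 5% test of non-inferiority is equivalent to asking whether the lower limit of a two-sided 90% interval lies above the margin. The lower limit of a two-sided 95% interval is a one-sided 2.5% test, which is stricter. The sizing section and the analysis section therefore point to different thresholds for the same primary conclusion.

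The other rule in {20a} does not settle the matter. As named, t and Mann-Whitney tests compare the arms for equality. A p-value below or above 0.05 from such a test says nothing about whether the difference exceeds -0.05.

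Two things are at stake. The same data could be called non-inferior under one section and not under the other, and the choice could be made after the results are known. Also, if the 95% interval is the deciding one, the trial has less power than it states.

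**Working it through.** **Inputs.** Control success 0.937, L-PRF success 0.95, margin 0.05, one-sided alpha 0.05, power 80%, 167 per arm evaluable and 175 per arm enrolled (all Sample size {14}); allocation "subjects randomized 1:1 in two parallel groups" (Trial design {8}).

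**Step 1: reproduce the stated size.** With unpooled variance,

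n per arm = (z_alpha + z_beta)² × [0.937 × 0.063 + 0.95 × 0.05] / (0.013 + 0.05)².

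The bracket is 0.059031 + 0.0475 = 0.106531. The denominator is 0.063² = 0.003969. Their ratio is 26.84.

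- One-sided 0.05: (1.645 + 0.842)² × 26.84 = 165.9, so 166 per arm against 167 stated. The plan's figure reproduces.
- One-sided 0.025: (1.960 + 0.842)² × 26.84 = 210.7, so 211 per arm.

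The 334 was therefore built on one-sided 0.05.

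**Step 2: power under each rule.** Power = Φ(0.063/SE − z), with SE = √(0.106531/n).

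- n = 167: SE = 0.02526 and 0.063/SE = 2.494. Power is Φ(2.494 − 1.645) = 80.2% at one-sided 0.05 and Φ(2.494 − 1.960) = 70.3% at 0.025.
- n = 175: SE = 0.02467 and 0.063/SE = 2.553. Power is 81.8% at 0.05 and 72.4% at 0.025.

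Exact binomial enumeration of the interval rule at the same rates gives:

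| Lower limit from | 167 per arm, 90% CI | 167 per arm, 95% CI | 175 per arm, 90% CI | 175 per arm, 95% CI |
|---|---|---|---|---|
| Wald | 80.8% | 70.6% | 81.9% | 72.8% |
| Newcombe | 78.9% | 67.3% | 80.1% | 69.0% |

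**Step 3: equal leak counts at the assumed rate.** A 6.3% leak rate implies 0.063 × 175 = 11.0 leaks per arm. With 11 leaks in each arm of 175, the difference is 0 and p = 164/175 = 0.9371.

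- Wald: SE = √(2 × 0.9371 × 0.0629/175) = 0.0259. The 90% lower limit is −1.645 × 0.02595 = −0.0427 (passes). The 95% lower limit is −1.960 × 0.02595 = −0.0509 (fails).
- Newcombe, built from the Wilson limits of each arm: at 90% the limits are 0.8998 and 0.9612, so the lower limit is −√(0.0373² + 0.0240²) = −0.0444 (passes). At 95% they are 0.8910 and 0.9645, so the lower limit is −√(0.0462² + 0.0274²) = −0.0537 (fails).

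The two rules split under either method. The same holds at 167 per arm: 10 against 10 leaks gives 90% limits of −0.0427 (Wald) and −0.0446 (Newcombe), and 95% limits of −0.0509 and −0.0541.

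**Sensitivity only.** If both arms truly have 93.7% success, normal-approximation power at 167 per arm is 59.3% at one-sided 0.05 and 46.8% at 0.025. This departs from the plan's disclosed planning assumption and is not part of the inconsistency.

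**The case against.** The strongest reply is that the only formal hypothesis and error rate are in Sample size {14}. The analysis section says that the difference will be reported with a 95% interval, not that this interval decides. Testing at one-sided 0.05 and reporting a conventional 95% interval can coexist, and on that reading power is 80.2%. Naming the bound and the interval method might also be left to the full protocol or the SAP.

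The first part stands: that the 95% interval decides is an inference, so the loss of power is conditional. The second part does not remove the point. The article itself states both a sizing level and a primary interval, they do not match, and it gives no other usable test of the margin.

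Stronger readings are tempting, and the article does not support them:

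- *The sample size is miscalculated.* It is not; 334 reproduces at the level stated for it.
- *The trial simply has 70% power.* That holds only if the 95% interval decides, which is never stated.
- *The 95% success rate for L-PRF comes from an excluded population.* The feasibility study behind it falls within a group of papers that the Background cites with emphasis on endonasal skull base work, and transsphenoidal surgery is excluded here. But that passage also speaks of craniectomies, and the Discussion cites the same study for feasibility of dural closure in neurosurgery generally. Its population cannot be established from the article.

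**Conclusion.** The point holds as an inconsistency between Sample size {14} and Statistical methods {20a}. The deciding bound for the primary endpoint is not fixed, and the two candidates give opposite answers at a result close to what the plan expects: 11 against 11 leaks in 175 per arm.

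If the one-sided 0.05 test decides, power is about 80% as stated. If the 95% interval decides, power is about 67 to 70% at 167 per arm and 69 to 72% at 175 per arm, depending on the interval method; 80% would have needed 211 per arm. These figures assume the plan's own rates (93.7% and 95%), the 0.05 margin, and complete primary outcome data at the stated numbers.

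It matters because this is the primary conclusion of a non-inferiority trial, and the Discussion's confidence in the sample size depends on which rule is used.

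**What to change.** Before results are seen, make the two sections agree. In {20a}, state that non-inferiority is concluded if the lower limit of a named interval, by a named method, for the difference in success rates (L-PRF minus control) lies above -0.05. State also that the general t or Mann-Whitney p < 0.05 rule does not apply to the primary endpoint. Then choose one of the following:

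- **(a) Keep the design as sized.** Leave one-sided 0.05 and 80% power in {14}. Name the two-sided 90% interval (or the one-sided 95% bound) as the decision interval, and label the 95% interval descriptive. This is the smaller change.
- **(b) Let the 95% interval decide.** State in {14} that 334 was derived at one-sided 0.05 and that power at one-sided 0.025 is about 67 to 70% (167 per arm) to 69 to 72% (175 per arm). Quote the figure for the method chosen: with Newcombe, 67.3% and 69.0%.

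Neither option needs more patients or changes any treatment. The cost is wording, filed as an amendment under the article's own procedure if the protocol text changes. Under (b) the stated power also becomes less favourable. The Trial status section describes recruitment as ongoing and no interim analysis is planned, so on the article's account the rule can still be fixed without knowledge of the results.

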### Recruitment {15}

In 2017, 400 patients underwent cranial surgery at UZ Leuven, and around 350 would have been potential candidates for this study. Considering the estimated enrollment rate of one out of three patients, we aimed to finish recruitment within 3 years. Due to the impact of the COVID-19 crisis, recruitment will be extended for one additional year. Patients will be recruited via the surgical tool of the electronic hospital record system. The planning tool is scanned weekly by the study coordinator and a list of probably eligible patients (all scheduled cranial surgeries) is presented to the surgeon. After agreement by the surgeon, the patients are informed about the study.

### Assignment of interventions: allocation

#### Sequence generation {16a}—concealment mechanism {16b}—implementation {16c}

Patients are randomized into two groups, i.e., one arm treated with commercially available fibrin sealants and the other arm treated with L-PRF. The randomization sequence is generated by the study coordinator using an online randomization tool (www.sealedenvelope.com), for simple randomization with two treatment groups of equal size, no blocks, and no stratification factors. The allocation list is then uploaded into the Research Data Capturing solution (RedCap), a system where access is restricted to the study personnel. Only one subject’s allocation can be released at a time, after confirming that the patient is suitable for randomization. Participants are enrolled by the study coordinator or his/her delegate. Randomization is done during surgery using the Randomize-tool in RedCap by trained study personnel, other than operating room staff, for example, the study coordinator. The arm to which the patient is allocated is communicated by telephone to the operation theater staff.

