L-PRF and liquid L-PRF glue are prepared during surgery. In all study subjects, L-PRF preparation is performed by the study coordinator to ensure protocol adherence. In this procedure, timing is particularly important to guarantee optimal membrane formation. Therefore, the arterial line is flushed, and immediately after, 20 mL of arterial blood is collected in a sterile syringe and transferred to two sterile 10-mL glass tubes (A-PRF®, Process for PRF, Nice, France), and instantaneously put in a centrifuge at 2700 rpm (400* g*) (IntraSpin®, Intra-Lock, Boca Raton, FL, USA). At the time of transfer to the glass tubes and start of centrifugation, a second 20-mL syringe is filled with arterial blood. The centrifugation process is interrupted as the second batch of collected blood is transferred to 10-mL glass tubes, to ensure precise timing to add the tubes into the centrifuge when decelerated. The centrifuge is instantly restarted at 2700 rpm for 12 min. If deemed necessary, one more 20-mL syringe can be collected to fill two more 10-mL glass tubes and added to the centrifuge in a similar fashion. After the centrifugation process, the tubes are inspected for the presence of a dense clot right above the red blood cell layer. If these are not present, the tubes are set aside for 10 min and inspected again. The tubes are opened and presented to the scrub nurse to remove the clot with sterile tweezers. The clot is placed in an Xpression Box® (Intra-Lock, Boca Raton, FL, USA) and gently compressed by placing the compression plate and the lid on top. After 5 min, the membranes are ready for surgical application by placing them on sutured dura. If necessary, the membranes can be left in the Xpression box® for up to 3 h until application.

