### Strategies to improve adherence to interventions {11c}

The study coordinator is present during the intervention to ensure adherence to the allocation. As the intervention is administered at a single time point during surgery, no further strategies for intervention adherence are necessary.

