### Assessment of interventions: blinding

#### Who will be blinded? {17}

The randomization is single-blinded, i.e., enrolled patients do not know which group they are allocated to. Blinding of surgical staff is not possible as L-PRF is clearly different from fibrin sealants. The bias of surgeons is reduced as much as possible by announcing the treatment arm only after the dural opening. Paramedics at the neurosurgery hospitalization department do not have access to the randomization code, thus reporting bias is reduced during hospital follow-up. Researcher’s bias is reduced by reblinding subject allocation after surgery. For analysis, group allocation will only be released after the statistical analysis has been performed.

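### The study coordinator both generates the allocation sequence and enrols participants, so concealment from the enroller is not assured, and the reblinding claim cannot cover that role

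*Protocol article*

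**What the plan says.** All references are to the protocol article.

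- **Generating the list.** Items 16a–c (sequence generation, concealment, implementation): "The randomization sequence is generated by the study coordinator using an online randomization tool". The method is simple 1:1 randomization without blocks or strata. The list is then uploaded to RedCap, to which only study personnel have access. Who uploads it is not said.
- **Finding candidates.** Recruitment {15}: "The planning tool is scanned weekly by the study coordinator". The resulting list covers all scheduled cranial operations and goes to the surgeon, who must agree before a patient is approached.
- **Enrolling.** Items 16a–c: "Participants are enrolled by the study coordinator or his/her delegate".
- **Releasing the allocation.** Items 16a–c: only one subject's "allocation can be released at a time, after confirming that the patient is suitable for randomization". Release takes place during surgery, "by trained study personnel, other than operating room staff, for example, the study coordinator", and the arm is telephoned to theatre.
- **Delivering the intervention.** Intervention description {11a}: "In all study subjects, L-PRF preparation is performed by the study coordinator to ensure protocol adherence". Strategies to improve adherence {11c}: "The study coordinator is present during the intervention to ensure adherence to the allocation".
- **Blinding.** Who will be blinded? {17}: researchers' "bias is reduced by reblinding subject allocation after surgery". The section does not say which researchers or by what means. Patients are blinded, and ward paramedics cannot see the code.
- **Data entry.** Item 18a: the materials used come from the neurosurgical report, postoperative data come from the hospital and outpatient records, and trained study personnel (a research assistant) transfer source data to RedCap.

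**The concern.** Concealment means that whoever enrols a patient, or judges the patient fit for randomization, cannot know which arm comes next. The usual safeguard is to separate the person who makes the list from the person who enrols. Here the article gives both tasks to one role and states no barrier between them.

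There is room for such knowledge to matter. Recruitment {15} expects about one patient in three to be enrolled. Item 26a has consent taken on admission, usually the day before elective surgery. Release in theatre depends on a confirmation of suitability. If the next arm can be known, any of these steps could come to depend on it.

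The second part concerns what happens after surgery. Item 17 relies on reblinding to limit researcher bias. The primary endpoint (Outcomes {12}) counts a leak as clinically relevant if, among other things, it leads to longer hospitalization or repeat imaging, which leaves some judgement in classification. A safeguard that cannot work for some of the people it appears to cover should not be relied on.

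**Working it through.** The point is about procedure and rests on no figure in the plan. For background, the sample size reproduces. With success rates 0.937 and 0.95, margin 0.05, one-sided alpha 0.05 and 80% power:

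n per arm = (0.937×0.063 + 0.95×0.05) × (1.645 + 0.842)² / (0.95 − 0.937 + 0.05)² = 165.9

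That is 166 per arm and 332 in total, against 334 stated.

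**Step 1: does any safeguard cover the list's author?**

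| Safeguard (items 16a–c) | Protects against | Covers the generator? |
|---|---|---|
| Release one at a time | Users who see the sequence only through RedCap | No |
| RedCap access limited to study personnel | People outside the study | No, the coordinator is study personnel |
| Simple, unblocked sequence | Guessing from past allocations (next arm stays at 50%) | No, the list gives the arm directly |
| Randomization during surgery | Surgeons and theatre staff knowing early | No |

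No section gives generation to an independent person or denies the coordinator access to the list.

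**Step 2: can the coordinator be reblinded?** Being present to ensure adherence to the allocation requires knowing the allocation. Item 11a can be read as preparation for every subject or only for those allocated to L-PRF; attendance reveals the arm either way. Reblinding therefore cannot hold for this role.

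**Step 3: data-entry staff.** Item 18a draws the materials used from the neurosurgical report, and these identify the arm. Anyone who enters both those data and the postoperative data can see the arm while entering leak status. The article does not separate the two tasks.

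**Step 4: scale, on stated assumptions.** The size of any bias cannot be derived from the document. Two illustrations:

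- *Steering.* Suppose three higher-risk patients are swapped with three lower-risk patients, 175 per arm. The expected difference moves by 6 × (excess risk)/175. With the Background rates of 5.8% infratentorial and 2.9% supratentorial: 6 × 0.029/175 = 0.1 point. With an extreme contrast of 17.2% (the no-sealant rate under Sample size) and 2.9%: 6 × 0.143/175 = 0.5 point.
- *Misclassified outcomes.* Each L-PRF leak not counted moves the estimate by 1/167 = 0.6 point. Take a true difference of exactly −5 points (88.7% v 93.7%), 167 per arm and k uncounted leaks. With b = k/167, p = 0.887 + b and s = √{[p(1−p) + 0.937×0.063]/167}, the one-sided error is 1 − Φ(1.645 − b/s). This gives 5.0% for k = 0, 7.4% for 1, 10.7% for 2 and 15.0% for 3.

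The second illustration shows why masked entry of leak status is worth having. It is not evidence that outcomes are being miscounted.

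**The case against.** The defence has real substance.

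- The article does not say that the coordinator keeps or consults the list. A reader might infer that allocation is known to the enroller, or that concealment has failed. The text does not show that; it shows only that nothing prevents it.
- The coordinator does not choose candidates alone. The list covers all scheduled cranial operations, the surgeon must agree, and the surgeon hears the arm only after dural opening. Enrolment may be delegated. The coordinator is only an example of who releases the allocation. The article does not say who uploads the list or who confirms suitability.
- A reader might call the trial open-label. It is single-blinded: patients do not know their arm, ward paramedics have no access to the code, and allocation is to be withheld until the analysis has been done.
- A reader might infer that the coordinator classifies leaks. No section says so; item 18a assigns data transfer to a research assistant.
- A reader might take three steered patients to move the estimate by 3/175 = 1.7 points, a third of the margin. That needs three whole outcomes to change. Steering moves only each patient's excess risk, about 0.1 point on the article's own rates.

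All of this limits the point. None of it separates generation from enrolment, or makes reblinding possible for someone who was present to oversee adherence to the allocation.

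**Conclusion.** The point holds in a limited form. The article makes one role both generator of the sequence and enroller, and its stated safeguards do not protect the sequence from its author. Concealment from the enroller is therefore not assured; no breach is shown. The reblinding claim cannot be true of the coordinator, is doubtful for staff who enter both materials and outcomes, and may still hold for staff uninvolved in surgery or in extracting operative data.

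No planned figure changes. Any effect through steering a few patients is likely to be small on the article's leak rates (0.1 point for three swapped patients, 0.5 point under an extreme assumption). Miscounted outcomes would matter more, but that route depends on who enters leak status and what they see, which the article leaves open. The conclusion assumes that the roles operate as the article states them, with no unreported bar on the coordinator's access. The change is worth making because it is cheap and because bias of this kind cannot be removed at analysis.

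**What to change.** 1. For all remaining patients, have someone already in post outside the trial team, such as the hospital's RedCap administrator or a statistics unit, generate and upload the list. The coordinator should have no access to it. Keep simple randomization: blocks or strata would not settle who holds the list, and with unblinded theatre staff blocks would make the next allocation easier to predict.
2. Have leak status entered by existing staff who were not in theatre and who do not use the operative report or materials log. Other existing staff enter the operative data.
3. Reword item 17 to say who is reblinded and how, and limit it to staff it can cover. The coordinator should not be among them.

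The cost is a short amendment, changed RedCap user rights and a split of data-entry tasks among existing staff. Recruitment began in January 2020 with completion estimated by December 2023, so the new list protects only patients still to be randomized. Earlier allocations must be reported as made under the old scheme. Masked entry of leak status can also cover patients already randomized whose outcome has not yet been entered.
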